### Recruitment {15}

We aim to recruit 484 participants in total (242 in each arm). We estimate that we will be able to reach this number in 3 influenza seasons. Should we be unable to recruit the necessary number of participants each year, enrollment could be prolonged for a fourth year. In case of a low number of influenza patients during future seasons, seasonal recruitment makes it relatively easy to organize the opening of new centers during spring/summer.

## Assignment of interventions: allocation

### Sequence generation {16a}

Patient randomization was performed by using randomization blocks of varying sizes. Randomization is stratified only by study site. One specific randomization list was prepared for each study site before the first influenza season started (in November 2024). The randomization lists cover all three influenza seasons and are 50% longer than the number of participants intended to be included. The pharmacist prepares treatment and placebo kits in advance, each having a randomization number. After study inclusion, kits are allocated to each patient following the order of inclusion.

### Concealment mechanism {16b}

The randomization list has been prepared by an external person to the study and has been only made accessible to the pharmacist of the Geneva University Hospitals who prepares the medication kits. Thus, the treatment allocation is concealed from patients, physicians, and trial statistician and all other involved study personal.

### Implementation {16c}

Randomization list generation was done by an expert in clinical trials who is not part of the study team. Dedicated nurses and study physicians oversee patient enrollment. Assignment to the intervention is done at randomization by the study nurse, who takes the next available kit prepared in advance by the Geneva University Hospitals pharmacist.

## Assignment of interventions: blinding

### Who is blinded {17a}

The study is triple-blind, with study participants, study nurse/physician, treating physician, and data analyst all blinded to the patients’ intervention group. Emergency unblinding is possible 24/7.

Baloxavir and placebo packaging are similar, ensuring the double blinding.

As mentioned above, the person in charge of creating the randomization list and the physician keeping a copy of the randomization list are not part of the study.

All unblinding events will be recorded as a deviation of the protocol in the TMF.

### Procedure for unblinding if needed {17b}

Unblinding is possible:In case of a life-threatening event suspected to be related to therapy (SAR or SUSAR).In case this information is needed by the treating physician to provide the best possible care for the patient.

The pharmacy at the Geneva University Hospitals keeps a copy of the randomization list in case of necessity for emergency unblinding, which is possible 24/7 by the pharmacist on duty.

As the treatment is only administered in a single dose, and does not preclude the administration of another antiviral active against influenza viruses, the need for emergency unblinding is very low.

## Data collection and management

### Plans for assessment and collection of outcomes {18a}

Primary outcome: We use the NEWS2 scoring system as a reliable and easily implementable method to evaluate disease severity at inclusion and to measure improvement in clinical status during follow-up. The primary outcome (NEWS2 score or hospital discharge) is recorded in the CRF once a day by dedicated study nurses. Components of the NEWS2 score are part of regular clinical management and therefore recorded by the team in charge of the patient during hospitalization. Death or ICU admission is not considered as discharge in the context of the primary endpoint. In case the patient is transferred to another hospital, it is considered as discharge regarding the primary endpoint. Transfers from the four participating university centers most often occur to rehabilitation hospitals, indicating that the patient no longer requires acute care for the influenza episode and is thus considered discharged.

To evaluate change in clinical status following treatment, we also use the 6-point ordinal clinical status severity scale. The remaining clinical outcomes include parameters which are easily measurable (need for O_2_ supplementation) or easily evaluable (need for antibiotic therapy for influenza complication, ICU admission, death). Influenza complications are retrieved from the discharge letter at the end of the hospital stay. The study nurses/physician collect the above data directly from the patients’ electronic medical records and enter it into the e-CRF. Clinical monitors will randomly check for data consistency and correctness.

Quality of life questionnaire EQ-5D-5L [17, 18] is filled out by the study nurses/physician on D0 and D90 post-treatment administration. At D90, the answers are collected by the study nurses/physician via the phone and are entered directly to the e-CRF. In case the patient is incapable of answering the questions, the questionnaire is not filled out.

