## Methods: participants, interventions and outcomes

### Study setting {9}

The trial is implemented in four large Swiss hospitals: Geneva University Hospitals; University Hospital Zurich; University Hospital Lausanne; Locarno and Lugano Regional Hospitals.

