### Outcomes {12}

#### Primary outcome

The primary outcome is time to clinical improvement (in hours), calculated from treatment administration until the measurement of a NEWS2 score ≤ 2 maintained for 24 h, or until hospital discharge, whichever comes first.

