#### Secondary clinical outcomes

Clinical status severity score (from 1 to 6) on day 7 post-treatment administrationDuration of hospitalization post-treatment administration (in hours)Duration of O_2_ supplementation post-treatment administration (in hours)In-hospital clinical failure, defined as death or ICU or intermediate care unit (ICMU) admission during hospitalization or up to 30 days post-treatment administration in case of prolonged hospital stayMortality at D90Influenza-related complications occurring between D0 and D90, diagnosed by the treating physician (composite outcome defined as pneumonia, sepsis, acute lung injury or acute respiratory distress syndrome (ARDS), encephalitis/encephalopathy, myo- or pericarditis, otitis, sinusitis as well as any cardiovascular event (cardiac decompensation, myocardial infarction, or stroke))Number of antibiotic days (AD) prescribed during hospitalization or up to 30 days post-treatment administration in case of longer hospital stayQuality of life at day 90 post-treatment administration. Questionnaire type: EQ-5D-5L

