### Plans to promote participant retention and complete follow-up {18b}

Subjects who withdraw or are withdrawn from the study prior to IMP administration will be replaced. No follow-up of these subjects will be performed, and no data will be analyzed. Subjects withdrawing or withdrawn after randomization and IMP administration will not be replaced. Data and samples collected before withdrawal will be analyzed. The reason for study discontinuation or deviation will be recorded in a specific section of the e-CRF.

Patients who drop out will be right censored at the time of withdrawal, with reasons for withdrawal documented. For deceased patients, clinical improvement will be considered as having never occurred until the end of follow-up: those patients will be right censored at 30 days.

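### Every transfer to another hospital counts as clinical improvement in the primary endpoint, so a patient moved to another acute or intermediate-care unit without having improved becomes an early success

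*Protocol article*

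**What the plan says.** The Primary outcome section of the protocol article measures time from treatment to a NEWS2 of 2 or less held for 24 hours, "or until hospital discharge, whichever comes first". Discharge alone is thus enough, at any NEWS2.

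The section on assessment and collection of outcomes {18a} says what discharge means. It first makes two exceptions: "Death or ICU admission is not considered as discharge in the context of the primary endpoint". It then adds: "In case the patient is transferred to another hospital, it is considered as discharge regarding the primary endpoint". The reason given is that "Transfers from the four participating university centers most often occur to rehabilitation hospitals", which the authors take to show that acute care for influenza is over.

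Three other places bear on this:

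- Study setting {9} lists the sites as "Geneva University Hospitals; University Hospital Zurich; University Hospital Lausanne; Locarno and Lugano Regional Hospitals".
- Secondary clinical outcomes has a separate failure outcome: "In-hospital clinical failure, defined as death or ICU or intermediate care unit (ICMU) admission during hospitalization".
- For patients who die, the retention section {18b} says that "those patients will be right censored at 30 days". The section on intercurrent events applies this composite handling to death before improvement, and transfer is not among the events it names.

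**The concern.** The rule is wider than its justification. Saying where transfers go in most cases concedes that some go elsewhere, yet all are scored alike. The justification also speaks of four university centers, whereas one of the four sites is "Locarno and Lugano Regional Hospitals", where a transfer to obtain more intensive care is at least plausible.

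What is at stake is the meaning of the primary event. A patient sent to another acute ward or intermediate-care unit while still unwell enters the analysis as an early improvement. If that patient then dies, the intercurrent-event section does not reach the death, because on paper improvement came first. The patients misclassified are those whose course the treatment is meant to change, so the number affected may differ by arm even in a blinded trial.

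**Working it through.** **1. The text, case by case**

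| Situation, NEWS2 still above 2 | Primary endpoint as written |
|---|---|
| ICU admission in the same hospital | Not discharge, no event |
| Transfer to rehabilitation | Discharge, event |
| Transfer to another acute ward | Discharge, event |
| Transfer to intermediate care elsewhere | Discharge, event (only death and ICU are excepted) |
| Transfer to another hospital's ICU | Two sentences apply and point opposite ways; neither is given priority |
| Acute transfer, then death | Event at transfer; the death is no longer a death before improvement |

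The fourth row sits badly with the protocol's own failure outcome, which treats intermediate-care admission as a bad result.

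**2. The plan's own figures**

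Inputs from Sample size {14}: medians 5.5 and 4 days, 30 days of follow-up, two-sided 0.05. Allocation is 1:1 (Trial design {8}).

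- Hazard ratio: 5.5 / 4 = 1.375.
- Probability of an event by day 30, exponential times: placebo 1 − exp(−ln 2 × 30/5.5) = 0.977; baloxavir 1 − exp(−ln 2 × 30/4) = 0.994; mean 0.986.
- Events for 90% power: Schoenfeld, 4(z₀.₉₇₅ + z₀.₉₀)² / (ln 1.375)² = 415; Freedman, (z₀.₉₇₅ + z₀.₉₀)² × (2.375/0.375)² = 422.
- Total N: 415 / 0.986 gives 421 and 422 / 0.986 gives 429. The plan states 432.
- Subgroup at 80% power: 315 (Schoenfeld) or 320 (Freedman). The plan states 322 (161 per arm), and 322 / (2/3) = 483 against 484.
- Power at 484: 93.6% (Schoenfeld) or 93.2% (Freedman). The plan states 93%.

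The sample size reproduces. It does not depend on the transfer rule.

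**3. What the rule could do**

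The protocol gives neither the rate nor the timing of acute transfers, so both are assumed here. Trials of 242 per arm were simulated with exponential improvement times and analysed with an unadjusted Cox model (2,000 to 3,000 trials per scenario). A random share of patients is transferred without having improved. They are scored either as events at transfer (the plan's rule) or as not improved and censored at day 30 (the plan's rule for death).

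- Set A: medians 133.5 and 97.5 h (97.5 h plus the plan's 36 h), transfers spread evenly over 12–96 h.
- Set B: medians 5.5 and 4 days, transfers spread evenly over days 0.5–3.

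| Set | Placebo / baloxavir share | Plan's rule: HR, power | Not improved: HR, power |
|---|---|---|---|
| A | 0 / 0 | 1.37, 93% | same |
| A | 1% / 0.5% | 1.36, 92% | – |
| A | 2% / 1% | 1.36, 90–91% | power 93% |
| A | 4% / 2% | 1.34, 89% | 1.39, 94% |
| A | 8% / 4% | 1.31, 84% | 1.42–1.43, 96–97% |
| B | 5% / 2.5% | 1.33, 88% | 1.40, 95% |
| B | 10% / 5% | 1.30, 81% | 1.44, 97% |
| B | 2% / 2% | 1.37, 92% | 1.32, 84% |
| A | 4% / 4% | 1.36, 92% | 1.28, 74% |
| B | 5% / 5% | 1.36, 92% | 1.27, 71% |
| A | 8% / 8% | 1.35, 90% | 1.23, 59% |

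Ranges are repeat runs. At 4% and 2%, about 242 × 0.04 ≈ 10 placebo and 242 × 0.02 ≈ 5 baloxavir patients are affected.

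In the under-72-hour subgroup (161 per arm, planned at 80%), set A gives 74% against 82% at 4%/2%, and 67% against 86% at 8%/4%.

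Two patterns follow. If baloxavir prevents deterioration, the rule hands placebo extra early events and pulls the hazard ratio toward 1. If deterioration is equal in the arms, the rule leaves the ratio near its no-transfer value, while scoring the same patients as not improved lowers it clearly.

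**The case against.** The rule is disclosed, reasoned and applied under blind, and the transfers in question may be rare. The protocol calls all its sites large hospitals, three are university hospitals, and patients needing ICU care, high-flow oxygen or non-invasive ventilation at randomization are excluded. If acute transfers came almost entirely from the one non-university site, and it enrolled a quarter of patients (an assumption), an overall placebo rate of 4% would mean 4 / 0.25 = 16% of its placebo patients, which is high. At 1–2% the effect on power is small. This stands as a limit on size. It does not repair the definition, and blinding does not equalise deterioration between arms.

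There are also safeguards. All primary-outcome data are checked {19}, and monitors verify the values behind the last two NEWS2 scores before discharge {23}. Patients transferred with a high NEWS2 could therefore be found. Finding them does not change how they are scored.

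Three stronger readings are tempting and are not supported:

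- A reader might infer that transfer to another hospital's ICU definitely counts as improvement. The ICU exception is not limited to the same hospital and may be meant to prevail. The text is contradictory here, not settled.
- A reader might infer that these patients also drop out of the in-hospital failure outcome. The transfer rule is confined to the primary endpoint, and the failure outcome is defined separately.
- A reader might infer that the rule always works against baloxavir, or hardly matters when rates are equal. With equal rates, the two scorings differ more in power than at 4%/2%, and the plan's rule gives the higher power.

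**Conclusion.** The point holds. As written, a transfer to another acute ward or intermediate-care unit without improvement is a primary-endpoint success, and the stated rationale neither covers such transfers nor describes all the sites. For ICU transfers the protocol contradicts itself. A later death in such a patient escapes the composite handling as the intercurrent-event section words it.

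The size is unknown, because no transfer rate is given. Under the assumed rates, the two scorings differ by 2 to 3 points of power at 2%/1%, about 5 points at 4%/2%, and 18 to 21 points in the other direction at an equal 4–5% per arm. These figures assume exponential times, early transfers and no covariate adjustment. The firm conclusion is that the result can move either way according to reasons for transfer that the rule ignores. The definition should therefore be settled before unblinding.

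**What to change.** In {18a} and the Primary outcome section:

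- Count a transfer as the event only when it is to rehabilitation or other non-acute care, or when a NEWS2 of 2 or less maintained for 24 hours is documented.
- Otherwise the transfer is not an event. Follow the patient through the receiving hospital's record where it can be obtained.
- Where it cannot, fix the handling in advance, for example not improved to day 30, as for death. That choice assumes the worst for missing data, so add sensitivity analyses with censoring at transfer and with the current rule.
- State explicitly how a transfer to another hospital's ICU is scored, so that the two adjacent sentences agree.
- Correct the description of the sites in the rationale.
- Record transfer destination and NEWS2 at transfer in the e-CRF, and apply the rule under blind to patients already enrolled.

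Cost: a protocol amendment, with the approvals and registry updates that {25} requires if it is substantial; one e-CRF field for destination (NEWS2 is already scheduled throughout the stay); and some record requests. Power may also fall if acute transfers prove equally common in both arms. The blinded sample size re-estimation after the second season is a natural place to look at the pooled acute-transfer rate.

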On the other hand, a recent systematic review and network meta-analysis of randomized controlled trials in children and adults, comparing NAI treatment to placebo (in children)/to standard of care or to each other (in adults), highlighted the uncertainty of the efficacy of NAI to lower the risk of mortality (risk difference: −18 to +4/1000) or admission to ICU, and concluded that treatment may shorten the duration of hospitalization (for oseltamivir: −1.63 days (95% CI: −2.81 to −0.45) (low level of evidence)) [12, 13]. In hospitalized patients, there is only one retrospective observational study assessing the clinical benefits of baloxavir, showing a significant 30-day all-cause mortality reduction in the baloxavir group compared to oseltamivir when treatment was administered within 48 h POS [14]. Combination antiviral therapies (baloxavir and NAI) could in theory increase clinical effectiveness via the cumulation of antiviral potency (additive or synergistic effects) as well as by reducing the risk of antiviral resistance [15]. However, one phase III multi-center randomized clinical trial in hospitalized adult patients failed to show a benefit in time to symptom alleviation when compared to NAI monotherapy [16]. Due to the lack of strong evidence, physicians remain divided over whether patients hospitalized with complicated influenza would benefit from antiviral administration and, if yes, for how long after symptom onset.

As the equipoise exists regarding treatment efficacy, a placebo-controlled trial is needed to fill in this knowledge gap.

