### Objectives {7}

Primary objective: To measure the clinical efficacy of single-dose baloxavir in shortening the time to clinical improvement compared to placebo in adult immunocompetent patients hospitalized for influenza irrespective of the duration of symptoms.

Co-primary objective: To measure the clinical efficacy of single-dose baloxavir in shortening the time to clinical improvement compared to placebo in the subgroup of adult immunocompetent patients hospitalized for influenza and treated less than 72 h POS. Secondary objectives: To assess baloxavir’s efficacy in decreasing the risk for and the duration of oxygen therapy related to the influenza episode, as well as its efficacy in preventing serious influenza-related complications; to measure its effects on viral-load kinetics including duration of infectiousness.

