### Participant timeline {13}

Patients will be followed up during hospitalization; data on clinical symptom severity, as well as flu complications (exacerbation of underlying disease, bacterial superinfection, need for ICU admission, death), antibiotic use, and duration of hospitalization will be collected. Nasopharyngeal swab for virological endpoints will be taken on day 0 and day 3 following treatment administration. After discharge, one phone follow-up visit is planned 90 days post-treatment administration (Table 1).

**Table 1 Tab1:** Patient timeline, screening, inclusion, treatment and follow-up schedule

**Study visit**	**1**	**0**	**2**	**3.1**	**3.2**	**3.3**	**3.4**	**3.5**	**3.6**	**3.7**	**3.8**	**3.9**	**3.10**	**4**	**5**
	**Screening**	**Consent**	**Allocation**	**In-hospital follow-up**											
**Timepoint**	Day −2 to D0	D0	D0	D1	D2	D3	D4	D5	D6	D7	D8	D9	…	Discharge day	D90
**Window (in days)**															±10
**Informed consent**		x													
**Inclusion and exclusion criteria**	x														
**Flu symptoms history**			x												
**Medical history**			x												
**Demographics**			x												
**Quality of life questionnaire**			x												x
**NEWS2 score**	x		x	1/8 h until discharge (a)											
**Clinical symptoms severity evaluation**			x	1/D until discharge											
**Influenza complications evaluation**			x	1/D until discharge											x
**6-point ordinal scale**										x					
**Serious adverse events***			x	During hospitalization											x
**Laboratory results collection**			x^b,c^	Once between D2 and D4^b,c^											
**RT-PCR NP swab**			x^d^			x^d^									
**Viral culture**			x^e^			x^e^									
**Viral type and subtype**			x												
**Screening for resistance-associated mutations**			x^f^			x^f^									
**Biobaking: serum sampling**			(x)							(x)					

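### As worded, the complications composite and the clinical-failure outcome can count conditions that were present before dosing, which would dilute the test of prevention

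*Protocol article*

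**What the plan says.** **Objective.** Objectives {7} lists, among the secondary aims, baloxavir's effect on oxygen therapy "as well as its efficacy in preventing serious influenza-related complications".

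**Who can enter.** Eligibility criteria {10} requires hospitalization, a positive RT-PCR and NEWS2 of at least 4. The exclusion for acute severity covers ICU care, high-flow oxygen and non-invasive ventilation at randomization. Pneumonia, sepsis, cardiac decompensation and intermediate care are not named. The only other route out is the investigator's judgment that taking part would put the patient at risk.

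**Complications outcome.** Secondary clinical outcomes, under Outcomes {12}, gives a "composite outcome defined as pneumonia, sepsis, acute lung injury or acute respiratory distress syndrome (ARDS") and further items, including "any cardiovascular event (cardiac decompensation, myocardial infarction, or stroke"). The window runs from D0 to D90, and the diagnosis is the treating physician's.

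**Source of the data.** Plans for assessment and collection of outcomes {18a} states: "Influenza complications are retrieved from the discharge letter at the end of the hospital stay". Table 1 in Participant timeline {13} has a row "Influenza complications evaluation", marked at allocation on D0, daily until discharge, and at D90.

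**Clinical failure.** The same outcome list has "In-hospital clinical failure, defined as death or ICU or intermediate care unit (ICMU) admission during hospitalization", or up to 30 days after treatment if the stay is prolonged.

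**Analysis.** Clinical secondary outcomes, under Statistical methods {20a}, compares both outcomes with a Cochran-Mantel-Haenszel test stratified on center. Baseline complication status and level of care do not enter.

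**The concern.** A test of prevention needs events that the drug could still have prevented. Here the entry criteria let in patients who already have a component of the composite, the window includes the day of entry, and the named source summarizes the stay from admission. Nothing stated separates a pneumonia diagnosed on D0 before the dose from one that arises after it.

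Clinical failure has a similar gap. Its latest end is tied to treatment administration, but its start is not, whereas the neighbouring durations of hospitalization and of oxygen supplementation are both measured from treatment. Hospitalized patients are screened from Day −2, so there can be hospital time before the dose. A patient moved to intermediate care in that time is still eligible unless on high-flow oxygen or non-invasive ventilation.

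Events fixed before dosing fall equally on both arms in expectation. They add noise and pull the relative risk toward 1. Reduction of severe complications is in the trial's title and comes first among the main secondary outcomes in the abstract. The abstract's discussion also says that if no clear benefit is shown, antiviral treatment of hospitalized patients could be reconsidered. A diluted comparison on complications would feed into that decision.

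**Working it through.** **The plan's own figures.** The documents give no event rate, effect size or power for either outcome, so there is no figure of theirs to reproduce on this point. The primary-endpoint figure does reproduce. With exponential medians of 5.5 and 4 days and 30 days of follow-up, the event probabilities are 0.977 and 0.994, mean 0.986. That gives 484 × 0.986 ≈ 477 events. With Freedman's formula, √477 × (0.375/2.375) − 1.96 ≈ 1.49, or power of 93%, as stated. This point does not touch that calculation.

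**Inputs for the illustration.** 242 per arm (Intervention description {11a}) and two-sided 0.05. Everything else is assumed: new-event risk 20% on placebo and 10% on baloxavir, and a share q of each arm with a component at entry that is counted.

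**Formulas.**
- Counted risk = q + (1 − q)·p, where p is the new-event risk among patients free of the condition at entry.
- Risk difference = (1 − q)·(p_placebo − p_baloxavir).
- Relative risk = [q + (1 − q)·p_baloxavir] / [q + (1 − q)·p_placebo].
- Power = Φ[(d − 1.96·SE0)/SE1], where d is the risk difference, SE0 the pooled and SE1 the unpooled standard error of the difference.

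**Worked case, q = 20%, entry conditions counted.** Placebo 0.20 + 0.80 × 0.20 = 0.36; baloxavir 0.20 + 0.80 × 0.10 = 0.28. Difference 0.08, relative risk 0.28/0.36 = 0.78. SE0 = √(0.32 × 0.68 × 2/242) = 0.0424. SE1 = √[(0.36 × 0.64 + 0.28 × 0.72)/242] = 0.0423. Power = Φ(−0.07) ≈ 47%.

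**Same case, only new events counted, everyone in the denominator.** 0.16 versus 0.08. Difference 0.08, relative risk 0.50. SE0 = 0.0295, SE1 = 0.0293. Power = Φ(0.75) ≈ 77%. This is cautious, because it lets patients with a component at entry contribute no new event at all.

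| q | Relative risk, entry conditions counted | Power, entry conditions counted | Power, new events only (relative risk 0.50) |
|---|---|---|---|
| 0% | 0.50 | 87% | 87% |
| 10% | 0.68 | 65% | 83% |
| 20% | 0.78 | 47% | 77% |
| 30% | 0.84 | 35% | 71% |
| 40% | 0.88 | 26% | 64% |

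The fair comparison is along a row. The 87% at q = 0 is not what a better definition would deliver in a population with q above zero. The risk difference over all patients is (1 − q) times the difference among those at risk under either definition. Counting only new events restores the relative risk and removes the noise.

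**Clinical failure, assumed 12% versus 6%, 5% already in intermediate care and counted.** 0.05 + 0.95 × 0.12 = 0.164; 0.05 + 0.95 × 0.06 = 0.107. Relative risk 0.65, power about 45%. With new admissions only (0.114 versus 0.057), power is about 61%.

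**Smaller effect, assumed 20% versus 15%.** Power is about 30% at q = 0. At q = 20% it is about 15% with entry conditions counted and 24% with new events only.

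**The case against.** The case on the other side has real weight.

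- The composite concerns complications that occur in the window. On an ordinary reading, a pneumonia established before D0 did not occur between D0 and D90. Likewise, an admission to intermediate care is an event and not a status.
- The D0 evaluation in Table 1 is what one would use to separate existing from new conditions, and the rule for using it could sit in the full protocol, the analysis plan or the e-CRF guide.
- The discharge letter is not the only source. The same section says that staff collect data from the electronic medical records, and Strategies to improve adherence {11c} allows record review for complications up to 90 days after treatment.
- Every rate in the illustration is assumed, and the protocol claims no power for these outcomes.

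Most of this stands, and it rules out a stronger reading. A reader might infer that every patient admitted with pneumonia will be counted as an event, and that a false finding of no effect on complications is likely. The text does not say the first, and without rates the second cannot be shown. The phrase "patients hospitalized with complicated influenza" in Background and rationale {6a} does not help: it is background and does not say how many entrants will have a listed component. The intermediate-care gap is also narrow, since it concerns only patients not on high-flow oxygen or non-invasive ventilation.

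The objection does not remove the ambiguity. The article does state a window, a list of components and a source, and this is more than silence. Together they leave open whether a condition found on D0 before dosing counts, and the start of clinical failure is not stated.

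**Conclusion.** The point holds as an ambiguity in two secondary outcomes. As worded, both can count conditions that predate dosing, and the outcome list, Table 1 and the data-collection section need to be reconciled. Because allocation is random and blinded, any such counting is expected to be equal between arms. Type I error and the primary endpoint are not affected. The cost is a relative risk pulled toward 1 and lost power.

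The size is unknown, because the documents give neither event rates nor prevalence at entry. Under the assumed halving of a 20% risk, the loss against a new-events definition is about 30 percentage points of power at 20% prevalence (47% against 77%) and 38 at 40% (26% against 64%). With a smaller true effect, power is low under either definition. This is an inexpensive improvement worth making and not a flaw that threatens the trial's main result.

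**What to change.** Reconcile Secondary clinical outcomes, Table 1 and Plans for assessment and collection of outcomes {18a} as follows.

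1. Count a composite component only if its onset is after treatment administration, judged component by component against the D0 evaluation already in Table 1. A patient with one component at D0 stays in the analysis and can still have an event on another.
2. State in advance how a distinct new event or a worsening counts in a patient who has that component at D0. Bacterial superinfection, which Participant timeline {13} lists among flu complications, is the obvious case. Without this rule, a later bacterial pneumonia in a patient with viral pneumonia at entry would be lost.
3. Take the event and its onset date from the scheduled daily evaluation and the medical record, with the discharge letter as confirmation.
4. Count ICU or intermediate-care admission as clinical failure only when it is a new admission after treatment administration.

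The cost is revised outcome wording, plus an onset date and a present-at-D0 flag in the e-CRF. The evaluations themselves are already scheduled. The downside is fewer counted events and a lower reported complication rate. Recruitment is planned to run through the 2026/2027 season and the analyst is blinded, so the change can be made without knowledge of allocation.
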